#### Review of Patient Records

Patient records were accessed from the facilities where the participants were attending ANC or where they gave birth. The patient folder contains the maternity case booklet and other related files, in which facility personnel record information from the patient’s antenatal visits, during labor, and after giving birth. Research assistants and the research team captured the following information from the maternity case booklet and its related files: clinical measures such as blood pressure at antenatal visits, dates of antenatal visits by pregnancy week, HIV and sexually transmitted disease testing, clinical measures from the labor process, and birth weight of the infant. The total number of antenatal visits was obtained from the recorded dates of antenatal visits by pregnancy week.

### Primary and Secondary Outcomes

The primary outcome variables for feasibility were the perceived satisfaction and user acceptability of the intervention, whereas the outcome variable for assessing initial preliminary efficacy was the number of antenatal appointments attended. The number of antenatal appointments attended was obtained from the patient records at the facility. A secondary approach was to code the number of antenatal appointments attended into a binary variable for <4 versus ≥4 visits to calculate the proportion of participants who attended the requisite of at least 4 appointments during pregnancy [17]. Secondary outcomes were awareness of HIV status, psychosocial determinants of antenatal appointment attendance (knowledge, risk perceptions, attitudes, self-efficacy, intentions, and action planning), perceptions of healthy pregnancy behaviors, number of intervention messages responded to, and variables evaluating the recruitment and study implementation processes.

### Statistical Analysis

Analyses will be conducted using SPSS (version 27.0; IBM Corp). Variables on perceived satisfaction with and acceptability of the Teen MomConnect messages and MI sessions in the evaluation section of the follow-up questionnaire as well as the number of messages responded to and MI attendance will be used for descriptive analyses to evaluate how the Teen MomConnect intervention was implemented and received. The outcomes of antenatal appointment attendance and its psychosocial determinants in the experimental (Teen MomConnect) and control (MomConnect) groups will be analyzed using linear regression for continuous outcomes and logistic regression for binary outcomes (including the outcome of percentage that attended ≥4 antenatal sessions) at follow-up. Covariates include age, race, previous pregnancies, school attendance, pregnancy week at enrollment, and exposure to MI. For outcomes related to knowledge, risk perceptions, attitudes, self-efficacy, intentions, and action planning scores that were measured at both baseline and follow-up, the change in mean values between baseline and follow-up in the experimental and control groups will be analyzed using analysis of covariance [46]. For each of these outcomes, moderation effects for race, gestational age at enrollment, socioeconomic status, age, and number of previous pregnancies will be tested with interaction terms in the regression models.

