The follow-up questionnaire included the same items as the baseline questionnaire and additional items assessing the outcome of the pregnancy. In addition, evaluation questions were included in the follow-up questionnaire that assessed the participants’ experiences with the SMS text messages and the motivational interview content, overall satisfaction with the study, and experiences with the research assistants. Specifically, 21 items evaluated the messaging component by measuring comprehension, tone, appropriateness, and content of the messages; the perceived degree to which the messages motivated behavior change; the frequency of receiving the messages; and whether participants were able to respond to the messages. The items evaluating the MI were administered to those who reported attending a session. A total of 17 items assessed the perceived degree to which the MI session motivated behavior change, with responses on a 5-point Likert scale.

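### Six psychosocial scores are assigned to two analyses with no stated priority, and perceptions of healthy pregnancy behaviours is left off the baseline-adjusted list

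*Protocol article*

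**What the plan says.** All places are in the Protocol article.

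- **First assignment (Statistical Analysis).** "The outcomes of antenatal appointment attendance and its psychosocial determinants in the experimental (Teen MomConnect) and control (MomConnect) groups will be analyzed using linear regression", with logistic regression for binary outcomes. The sentence ends "including the outcome of percentage that attended ≥4 antenatal sessions) at follow-up".
- **Covariates (same section).** "Covariates include age, race, previous pregnancies, school attendance, pregnancy week at enrollment, and exposure to MI". No baseline value of the outcome is listed.
- **Second assignment (same section).** The sentence opens by naming its scope: "For outcomes related to knowledge, risk perceptions, attitudes, self-efficacy, intentions, and action planning scores that were measured at both baseline and follow-up". Its main clause then gives the method used on those scores: "the change in mean values between baseline and follow-up in the experimental and control groups will be analyzed using analysis of covariance".
- **Outcome definitions (Primary and Secondary Outcomes).** "Secondary outcomes were awareness of HIV status, psychosocial determinants of antenatal appointment attendance". The bracket that follows defines the psychosocial determinants as knowledge, risk perceptions, attitudes, self-efficacy, intentions and action planning. Perceptions of healthy pregnancy behaviours is listed after that, as a separate secondary outcome.
- **Measurement (Questionnaires).** The baseline questionnaire covered perceptions of healthy pregnancy behaviours. For HIV it names knowledge and testing. Of the second questionnaire the section says: "The follow-up questionnaire included the same items as the baseline questionnaire".

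**The concern.** The six constructs in the ANCOVA sentence are the same six that define the psychosocial determinants in the regression sentence. Each score therefore falls under two models, and nothing says that one replaces the other or which result is the effect estimate.

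The two models can differ by more than precision. The regression covariates include exposure to MI. That exposure arises after randomisation and was planned only for the experimental group, with sessions held until 30% of the sample had received one (Recruitment Procedure). Conditioning on it moves the arm coefficient away from the total effect of the package. The ANCOVA sentence names no covariates. The section then tests moderation through interaction terms in the regression models, without saying which of the two models is meant.

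Perceptions of healthy pregnancy behaviours meets the plan's own criterion for ANCOVA, measurement at both time points, yet is not on the list. The regression sentence does not cover it either, because it is defined separately from the psychosocial determinants.

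At stake are power on the secondary outcomes, clarity about which estimate is reported, and a modest rise in false positives if the choice stays open until results are seen.

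**Working it through.** **1. The plan's own figure.** Study Design states power of at least 0.80 for d = 0.52/1.3 = 0.40 with 100 per group. With two-sided alpha 0.05 (assumed; not stated), z = 0.40 × √(100/2) − 1.960 = 2.828 − 1.960 = 0.868, so power is 0.807 (0.804 with the t distribution). The figure reproduces. It concerns attendance, which this point does not touch.

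**2. Which outcome goes to which model.**

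| Secondary outcome | Follow-up regression | ANCOVA of change | Baseline value |
|---|---|---|---|
| Knowledge, risk perceptions, attitudes, self-efficacy, intentions, action planning | yes, as psychosocial determinants | yes, by name | yes |
| Perceptions of healthy pregnancy behaviours | not named | not named | yes |
| Awareness of HIV status | not named | not named | not established; only HIV knowledge and testing are mentioned |

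Row 1 is a complete overlap. Row 2 is an outcome that fits the ANCOVA criterion but was left out.

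**3. Precision.** Inputs: 256 follow-up questionnaires (Results). Let r be the baseline to follow-up correlation given the other covariates. It is not in the article, so 0.3 to 0.6 is assumed. For a linear model, residual variance is multiplied by 1 − r², and the equivalent number of completers is 256/(1 − r²).

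| r | 1 − r² | Variance reduction | Equivalent completers |
|---|---|---|---|
| 0.3 | 0.91 | 9% | 281 |
| 0.5 | 0.75 | 25% | 341 |
| 0.6 | 0.64 | 36% | 400 |

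Splitting the 256 in proportion to the arms (256 × 219/412 ≈ 136 and 120; the actual split is not given), the smallest standardised difference detectable with 80% power without the baseline score is (1.960 + 0.842) × √(1/136 + 1/120) = 0.351. With it, this is multiplied by √(1 − r²): 0.335 at r = 0.3, 0.304 at r = 0.5 and 0.281 at r = 0.6. Power for d = 0.30 is 0.67 without the baseline score, and 0.71, 0.79 and 0.85 with it.

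**4. Two analyses per score.** Under the null, the follow-up-only and baseline-adjusted estimates correlate √(1 − r²): 0.954, 0.866 and 0.800. With both test statistics bivariate normal, the probability that at least one exceeds 1.960 in absolute value is:

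| r | P(either significant) |
|---|---|
| 0.3 | 0.064 |
| 0.5 | 0.073 |
| 0.6 | 0.078 |

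This treats the two models as differing only in the baseline score. It applies only if either result may count as positive.

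**The case against.** **General rule, then specific rule.** The first sentence may only give the model family by outcome type, with ANCOVA then replacing it for scores measured twice. The covariate list is introduced as what is included and need not be exhaustive. This is a natural reading, and ANCOVA is the better of the two analyses. But the text does not say that it replaces the regression, and the regression sentence names the psychosocial determinants explicitly. What stands is that the article states no intention to report two P values per score or to quote the better one. The 6.4% to 7.8% is therefore conditional.

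**HIV-status awareness.** A reader might infer that HIV-status awareness and perceptions were assigned models that ignore an available baseline value. The article does not support that, since it names no model for either outcome. For HIV awareness even the baseline value is an inference: the questionnaire description mentions HIV testing, not awareness of status, and the questionnaire itself is in an appendix that is not shown. Leaving the model for this outcome to a fuller plan is acceptable in a condensed article.

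**Bias.** A reader might also infer that leaving out the baseline score biases the comparison. Under randomisation the cost is mainly precision. Gestational week, the one characteristic in Table 2 that differed significantly between groups (P=.002), is already a covariate, and no baseline imbalance in a psychosocial score is shown. With 256 of 412 (62.1%) completing follow-up, balance among completers is not guaranteed. That is a further reason to adjust, but it does not demonstrate bias.

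**Size.** The regression is not unadjusted, as it has six listed covariates, so the gain depends on the partial correlation. The variance formula is for linear models and does not carry over to logistic regression. Both limits are accepted here.

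**Conclusion.** The point holds in a limited form. Six secondary scores are assigned to both a follow-up regression without a listed baseline score and an ANCOVA of change, with no priority. Perceptions of healthy pregnancy behaviours meets the plan's criterion for ANCOVA but is not included and has no named model.

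The gain from correcting this is a 9% to 36% lower residual variance and one reported estimate per score. That range assumes a correlation of 0.3 to 0.6 given the other covariates. The type I error of about 6.4% to 7.8% rests on the same assumption, and also on either analysis being allowed to count, which the article does not say.

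The correction is worth making because it is nearly free, but its reach is limited to secondary outcomes in a pilot. The attendance outcome and the sample size are unaffected.

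**What to change.** In Statistical Analysis:

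1. Name one main model for each of the six psychosocial scores: linear ANCOVA of the follow-up value on arm, the baseline value of the same score and the pre-specified baseline covariates. Exposure to MI should not be in this model, because it arises after randomisation. With the baseline score in the model, analysing change or the follow-up value gives the same arm estimate, so the planned ANCOVA needs only this clarification.
2. Drop the follow-up-only regression for these scores, and state that the moderation interactions are fitted in the ANCOVA.
3. Add perceptions of healthy pregnancy behaviours to the ANCOVA list.
4. For awareness of HIV status, say whether it was measured at baseline. If it was, use logistic regression with baseline awareness as a covariate, after checking that the model can be fitted if nearly all participants already aware at baseline remain so. If it was not, say so and make no baseline adjustment.

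The cost is a few sentences. The questionnaire data are already collected, and the article describes the analyses as still to be done.

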### Data Management, Confidentiality, and Privacy Protection

The data from Qualtrics were protected by log-in ID and password. The server that stored data on message sends and responses was password protected. The data were sent to the statistician and principal investigator upon study completion. The consent forms are kept in a locked storeroom.

### Quality Assurance

Practical training on recruitment and data collection procedures, with refresher sessions, was provided to the research assistants throughout the study to ensure its validity and accuracy. The baseline and follow-up data collected were checked for possible errors an average of every 2 weeks. The research assistants encouraged participants to ask questions about any concerns they had with the study. The research team monitored the study to oversee its progress. The research assistants provided feedback to the project manager 3 to 4 times per week on the study progress and any barriers encountered.

## Results

Recruitment of participants was conducted from May 2018 to December 2018. A total of 412 eligible participants were enrolled in this trial (Table 2). The participant characteristics did not differ significantly between the experimental and control groups, with the exception of average gestational week (control group: 23.1, SD 7.69; experimental group: 20.8, SD 6.76; *P*=.002). The mean age was 18.0 (SD 1.56) years; 36.2% (149/412) were attending an educational institution, 75.4% (307/407) lived in formal dwellings, 59.6% (242/406) reported household shortages of important items, and 10.9% (45/412) had been pregnant before. Of the 412 enrolled participants, 256 (62.1%) completed the follow-up questionnaire. Patient records were able to be retrieved for 54.4% (224/412) of the participants. Results on the preliminary efficacy and acceptability of the intervention will be disseminated via publications and conference proceedings throughout 2023.

**Table 2 table2:** Characteristics of the sample at baseline (n=412)^a^.

			Control (n=219)		Intervention (n=193)		Total sample		*P* value^b^	
Age (years), mean (SD)			18.1 (1.49)		17.9 (1.64)		18.0 (1.56)		.21	
Gestational age (weeks), mean (SD)			23.1 (7.69)		20.8 (6.76)		22.0 (7.35)		.002	
**Racial group^c,d^, n (%)**										.29
	Black African	59 (27.2)		64 (33.2)		123 (30)				
	Coloured	157 (72.4)		128 (66.3)		285 (69.5)				
	Other	1 (0.5)		1 (0.5)		2 (0.5)				
**Attending an educational institution, n (%)**										.29
	Do not attend educational institution	145 (66.2)		118 (61.1)		263 (63.8)				
	Attend educational institution	74 (33.8)		75 (38.9)		149 (36.2)				
**Dwelling type^e^, n (%)**										.79
	Informal	54 (25.1)		46 (24)		100 (24.6)				
	Formal	161 (74.9)		146 (76)		307 (75.4)				
**Self-perceived cost of living^f^, n (%)**										.12
	Food and clothes shortage	41 (19.2)		51 (26.6)		92 (22.7)				
	Shortage of other important things	78 (36.5)		72 (37.5)		150 (36.9)				
	Have important basics	95 (44.4)		69 (35.9)		164 (40.4)				
**Had been pregnant before, n (%)**										.73
	Yes	25 (11.4)		20 (10.4)		45 (10.9)				
	No	194 (88.6)		173 (89.6)		367 (89.1)				

^a^Counts do not always sum to 412 due to missing observations for some variables.

^b^Testing the difference in estimates between the control and intervention groups using chi-square tests for categorical variables and 2-tailed *t* tests for continuous variables.

^c^Control group: n=217; total sample: n=410.

^d^Race was self-reported by participants. Racial categories provided in the questionnaire were according to Statistics South Africa’s standard population groups: Black African, Coloured, White, and Indian. The White and Indian categories were collapsed for analysis due to small sample sizes. Race was reported not with the intention of reifying sociocultural constructs but rather to study ongoing health disparities across groups.

^e^Control group: n=215; intervention group: n=192; total sample: n=407.

^f^Control group: n=214; intervention group: n=192; total sample: n=406.

## Discussion

### Synopsis

This paper describes the development of the Teen MomConnect intervention and the protocol for the pilot RCT to measure its feasibility and preliminary efficacy. The intervention aimed to improve antenatal appointment attendance among pregnant adolescent girls and young women using tailored 2-way messaging and MI. The results of the pilot study will inform policy makers and health program officers on how tailored, age-appropriate, and motivational health behavior messages can be delivered via mobile phone to large numbers of young people. The intervention expands the messaging content of the MomConnect program, which already has high coverage, to be relevant to youth. If the intervention shows promising results (eg, in terms of feasibility), it can be tested in a formal, fully powered trial. The findings will also show how the intervention was implemented and inform how it can be improved in the future.

### Implementational Challenges

This study is subject to some foreseen implementational challenges. mHealth interventions often have high dropout rates, especially among young people. This study aimed to mitigate this by allowing for oversampling of baseline participants. This study will assess retention between baseline and follow-up, and the evaluation can inform retention strategies in future mHealth studies with adolescents. Second, many individuals in South Africa frequently change their mobile phone numbers, and this is expected to be common among adolescents and young adults. Studies on the MomConnect program found that messages were not delivered to a large number of users, which was attributed to users having changed their phone numbers [28]. This study was subject to the same problems. Future mHealth programs, particularly those designed for adolescents, can use smartphone apps rather than SMS text messaging–based systems. Nevertheless, SMS text messages were the most practical delivery option for this study as they facilitated comparison with the MomConnect SMS text message delivery and SMS text messages can reach all mobile phone users regardless of whether they have a smartphone and have no added costs to the user. This is particularly relevant in LMICs such as South Africa that experience challenges with mobile data costs, speed, and coverage [47]. Third, capturing information on the number of appointments attended is subject to the availability and ease of accessibility of the patient health records and the accuracy with which this information is captured by personnel at the facility. Therefore, the research team included questions on whether the participants attended all their appointments in the follow-up questionnaire. This question, although subject to self-report bias, can be used to supplement the analyses of appointment attendance.

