### Recruitment Procedure

A total of 20 trained research assistants conducted recruitment and data collection activities. Recruited participants received information sheets that described the objectives, benefits, and potential risks of the study; the dissemination of findings; the privacy and confidentiality of the study; and their right to withdraw from the study at any time. The participants were asked to complete a consent form (for participants aged ≥18 years) or assent form (for participants aged <18 years) before being enrolled in the study. In addition, parental consent forms were required for participants aged <18 years. Consenting individuals completed a self-administered baseline questionnaire on an electronic tablet or mobile phone. Baseline questionnaire completion was facilitated by the research assistants. In a few cases in which the participant was not comfortable with completing the questionnaire themselves, the research assistant administered the questionnaire. The questionnaire took approximately an hour to complete. Participants received a US $3 incentive for questionnaire completion.

User registration to receive the MomConnect and Teen MomConnect messages required information to be entered on the name, mobile phone number, age, language, and expected date of delivery (EDD) of users. These variables, as well as the estimated last menstrual date (LMD) and current enrollment in MomConnect, were extracted from the baseline data. In the few cases in which the participant did not have their own mobile phone, they were advised to enter into the baseline survey the mobile phone number of someone whom they lived with and whose mobile phone they could use to access the messages sent during the study. The EDD was required as messages are dependent on pregnancy week. In cases in which the EDD was missing, an estimate was calculated using the reported LMD. In cases in which both dates were missing, the participant was contacted telephonically several times to try to obtain either their EDD or LMD. The language was asked to assess the language in which participants would receive their messages. The options were English, Afrikaans, and isiXhosa. Participants were excluded from enrollment in the intervention study if one or more of their EDD, language, name, age, and mobile phone number was missing or if they were already registered on MomConnect.

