**Figure 1 figure1:**
[figure not shown]
Diagram of the study procedure. AGYW: adolescent girls and young women; EDD: expected date of delivery; MI: motivational interviewing.

The research assistants contacted participants from September 2018 to December 2018 to schedule MI sessions at times that were convenient for them. Preliminary interview sessions revealed that some participants did not answer their phones, many scheduled sessions but did not attend them, many could not make time to attend a session because of school and other commitments, and it was difficult to allocate participants to times when all group members were available. Therefore, based on the ascertained limited availability of participants between enrollment into the study and the end of their pregnancy, it was decided to conduct motivational interviews with participants until 30% of the sample had received an interview session. Interview sessions could be conducted one-on-one or in groups of up to 5 people. Participants received an incentive of US $6 for attending a session.

Once the EDD had passed, participants in both the experimental and control groups were programmed to receive the standard postpartum messages that users receive in the MomConnect program. Participants were contacted a week after their EDD had passed to schedule voluntary completion of the follow-up questionnaire. Participants who had an abortion, miscarriage, or stillbirth were also contacted. As with the baseline questionnaire, participants completed the follow-up questionnaire on an electronic device facilitated by the research assistants, and they received a US $3 incentive. Electronic administration of both the baseline and follow-up surveys was facilitated using the Qualtrics electronic survey tool (Qualtrics International Inc) [43].

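### The primary feasibility ratings come only from follow-up completers, among whom women the messages did not reach are probably under-represented, and the plan includes no check of this

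*Protocol article*

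**What the plan says.** Under Primary and Secondary Outcomes the article states: "The primary outcome variables for feasibility were the perceived satisfaction and user acceptability of the intervention". Statistical Analysis gives their source. The satisfaction and acceptability variables "in the evaluation section of the follow-up questionnaire as well as the number of messages responded to and MI attendance will be used for descriptive" reporting. Under Questionnaires, the evaluation items at follow-up include how often messages arrived and whether the woman could reply to them.

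The follow-up questionnaire is reached as follows (Recruitment Procedure, text after Figure 1): "Participants were contacted a week after their EDD had passed to schedule voluntary completion of the follow-up questionnaire". The mode of that contact is not given. Results reports the yield: "Of the 412 enrolled participants, 256 (62.1%) completed the follow-up questionnaire". No split by arm is given.

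On delivery, Implementational Challenges expects number changes to be common at this age. It recalls that in studies of the parent programme "messages were not delivered to a large number of users, which was attributed to users having changed their phone numbers", and adds that this trial faced the same problem. Its answer to dropout is to oversample at baseline and to assess retention.

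Some data do not depend on follow-up. The number of messages responded to and attendance at motivational interviewing (MI) are to be described, and under Data Management: "The server that stored data on message sends and responses was password protected".

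**The concern.** A lost or changed phone number can do two things: stop the messages arriving, and make the woman harder to find when the questionnaire falls due. If so, the women best placed to report that delivery failed are less likely to be in the data that rate the intervention. Both the ratings and the items on receipt would then lean towards women for whom the channel worked.

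The stated remedies do not fit this threat. Oversampling gives more completers but leaves the mix of reached and unreached women among them unchanged. A retention rate says how many women were lost, not whether they were the ones the messages failed to reach.

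This matters because the Synopsis names feasibility as an example of the promising results that would justify a fully powered trial, and says the results will inform policy makers about mobile delivery to large numbers of young people. Reach is part of that question.

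**Working it through.** **1. Reproducing the plan's figure.** Completion = 256/412 = 0.6214, or 62.1% as stated. Missing = 412 − 256 = 156, and 156/412 = 37.9%.

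**2. Is a common cause documented?**
- The registration fields (Recruitment Procedure) are name, mobile number, age, language and EDD. The mobile number is the only contact detail among them.
- When dates were missing, "the participant was contacted telephonically several times to try to obtain either their EDD or LMD".
- When MI sessions were being arranged, "some participants did not answer their phones".
- For the contact after the EDD, no mode is stated.

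Phone contact after baseline is therefore documented twice, and for the follow-up contact it is an inference.

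**3. Why oversampling does not help.** Let q be the true share of women not reached by messages, and r their chance of completing follow-up relative to women who were reached. The share of unreached women among completers is q·r / (q·r + 1 − q). Sample size does not appear in it. The document gives neither q nor r, so these are assumed values:

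| q | r = 1 | r = 0.5 | r = 0.25 | r = 0 |
|---|---|---|---|---|
| 10% | 10% | 5.3% | 2.7% | 0% |
| 20% | 20% | 11.1% | 5.9% | 0% |
| 30% | 30% | 17.6% | 9.7% | 0% |

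For example, with q = 0.20 and r = 0.5: 0.10/(0.10 + 0.80) = 11.1%. Unreached women vanish from the ratings only at r = 0.

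**4. The right denominator.** Acceptability of Teen MomConnect concerns the experimental arm, n = 193 (Table 2). Its number of completers is not reported. Arithmetic alone fixes it only between 256 − 219 = 37 and 193. If retention matched the overall figure, it would be 193 × 0.6214 ≈ 120.

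**5. Illustrative bounds.** Let f = 0.6214 and let s be satisfaction among completers (assumed). The worst case counts every non-completer as not satisfied: s·f. The best case counts every one as satisfied: s·f + (1 − f).

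| s | worst case | best case |
|---|---|---|
| 70% | 43.5% | 81.4% |
| 80% | 49.7% | 87.6% |
| 90% | 55.9% | 93.8% |

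For s = 80%: 0.80 × 0.6214 = 0.497, and 0.497 + 0.379 = 0.876. In women, with 120 completers of whom 96 are satisfied and 73 non-completers, this is 96/193 = 49.7% and (96 + 73)/193 = 87.6%. In between, suppose half of the non-completers were unreached and counted as not satisfied, and the rest resembled completers: 0.497 + 0.379 × 0.5 × 0.80 = 0.649, about 65%.

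These bounds describe missing ratings for any reason. They do not estimate the effect of changed numbers.

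**The case against.** A reader might infer that a changed number blocks both the messages and the follow-up, so that every woman with failed delivery leaves the feasibility result and the problem goes unmeasured. The document does not support that, for four reasons.

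- **Contact mode.** How women were contacted after the EDD is not stated. Recruitment used clinics and community networks, records were reviewed at facilities, and some women gave the number of someone they lived with. A changed number probably hinders follow-up, but a complete block is not shown.
- **Other feasibility measures.** Message replies, MI attendance, recruitment and implementation variables, and retention do not need a completed questionnaire. Only satisfaction and acceptability do. Women with failed or partial delivery who did complete follow-up can report it.
- **Server data.** The article says sends and responses were stored. It does not say that delivery was recorded or that every randomised woman is covered. No reply does not prove non-delivery either: most messages (48 static ones) ask for none, and the logic flow under Messaging Content sends feedback even to women who stay silent.
- **Denominator.** Bounds on all 412 women do not describe an outcome that concerns 193.

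All four objections stand, and they narrow the point. It can also be said that comparing completers with non-completers is detail a journal article leaves to the analysis plan, and that satisfaction is hard to define for a woman who received nothing. The first has some force. But the article does state its remedy for dropout, and that remedy does not address selection into the ratings. The second is a reason to present bounds as a sensitivity display and not as the main result.

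**Conclusion.** The point holds in a limited form. The primary feasibility ratings exist only for follow-up completers, 62.1% overall, with the experimental-arm figure unreported. Given the article's own account of changed numbers and its documented use of the phone for later contact, women the messages did not reach are probably under-represented in those ratings. Neither oversampling nor a retention rate corrects this. Reply counts and MI attendance are available without follow-up, but Statistical Analysis does not use them to check who is missing from the ratings.

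The direction is plausible, not proven, and the size cannot be derived from the document. The range of 49.7% to 87.6% is an illustration. It assumes 80% satisfaction among completers, and it applies to the experimental arm only if retention there was 62.1%. No formal progression rule rests on the ratings, so what is at stake is an over-favourable reading of feasibility. The point is worth acting on because the analyses were still to be done when the article was written.

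**What to change.** In Statistical Analysis, state that:

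1. Satisfaction and acceptability are reported with the experimental-arm denominator (n = 193) and the number of completers in that arm, with best-case and worst-case bounds beside the completer figure as a sensitivity display.
2. For all experimental women with server data, out of the 193, the proportion with at least one reply is reported, labelled as a lower bound on reach because silence does not prove non-delivery.
3. That proportion is compared between follow-up completers and non-completers in the experimental arm.

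This uses data already collected. The cost is a little more analysis and a less favourable headline acceptability figure.
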